
#### Proposed study rationale

The RESET-ASDH investigators propose a randomized controlled trial on the role of early neurosurgical hematoma evacuation versus non-operative management in elderly patients with a traumatic ASDH. The research group acknowledges that there is a particular subgroup of patients presenting with very poor clinical and radiological parameters, in which randomization of treatment may not be ethically justifiable. The fact that the ethical desirability of surgery in these severely injured patients may be questionable given the high chance of death or unfavorable outcome (which is the reason for some neurosurgeons to opt for conservative management of the aforementioned patient in case 2), does not change that conservative management of these patients equals imminent death. Questioning the effectiveness of surgery in these patients has been compared to questioning the effectiveness of a parachute in jumping out of a plane [55, 56]. Therefore, the most severely injured (defined as a GCS < 9) patients are, in the opinion of the researchers, unsuited for randomization and will not be included in this study with the exception of a specific subgroup described next. There is a category of comatose ASDH patients with a relatively small hematoma less than 10 mm thick and with less than 5 mm midline brainshift and no extracranial explanations for their coma (e.g., internal or external hemorrhages resulting in hypovolemia, hormonal or electrolyte imbalances, infections, and toxic substances) as assessed by the treating staff neurosurgeon. The most likely explanation is diffuse brain injury, not (yet) apparent on a CT scan. The surgical challenge lies in the decision to evacuate the hematoma in an emergency operation with the possibility that the hematoma is not the main explanation for the increased ICP or comatose condition. The BTF guidelines recognize this dilemma and point out that a prospective study should compare an aggressive strategy versus non-operative management (with the possibility of secondary surgery after neurological deterioration) in these comatose patients. Hence, an important subgroup of comatose patients with a small traumatic ASDH < 10 mm and a midline shift < 5 mm will be included in the randomized study.

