### Intervention description {11a}

#### Study procedures

##### Early surgical hematoma evacuation (group A)

Patients randomized to group A will undergo rapid (preferably within 1 to 2 h after randomization with a maximum of 8 h) neurosurgical evacuation of the ASDH with or without decompressive craniectomy (DC) (i.e., leaving out the bone flap). Generally in Europe, a craniotomy is performed for hematoma evacuation and DC when (intractable) swelling is seen intra-operatively or when swelling is expected (preventive). The general techniques are described below:*“After induction of general endotracheal anesthesia the patient is positioned on the back with the head placed in a lateral position with the unaffected side towards the ground. The head is secured in a three-pin Mayfield skull clamp. After the scalp is appropriately sterilized and draped, a curvilinear incision is made through all tissue layers to allow exposure of the appropriate entry on the skull bone. The skin- and muscle flap are lifted off the bone and folded frontobasally. Burrholes are made with the electrical drill and a boneflap is formed with the craniotome or a Gigli-saw by connecting the burrholes. The dura is cut along the bone edges. Next, the ASDH presents itself and is removed from beneath the dura in all corners. The removal of the hematoma may be facilitated by irrigation with water. After removal of the hematoma to the satisfaction of the surgeon’s discretion, hemostatic measures are taken with coagulation of potentially present bleeding cortical veins. Retractors are removed and the dura is closed with sutures. In case no DC is performed, the bone flap is replaced back in its original confines and secured to the skull with titanium plates and screws or with sutures. In some cases, a drain is placed under the skin for drainage of blood or fluid from the surgical area. The muscles and skin are sutured back together. A turban-like or soft adhesive dressing is applied. Generally magnifying loupes are used on the discretion of the surgeon. In the event of DC, the bone defect is generally made larger and the resulting bone flap will not be replaced. A bone flap of at least 11 cm anteroposterior (AP) diameter is raised. The decision for a DC can be made primarily or secondarily by increasing the defect of the bone flap that is formed during a normal craniotomy. In most cases this will be a unilateral frontotemporal, a parietal or a wide frontotemporoparietal craniectomy. Further surgical options are the replacement of (a portion of) the dura with autologous fascia, homologous tissue or synthetic material, and applied as a sutured graft or as an onlay. These nearly similar techniques are left to decide on the discretion of the surgeon. In conjunction to these surgical procedures the neurosurgeon can decide to place an intracranial pressure (ICP) monitor. The ICP device can be an intraparenchymal sensor or an extraventricular drain with a transducer for the ICP. The latter has an option to drain CSF (and thereby lower ICP). On a standardized form will be noted which technique is used and what the main findings were during surgery.”*

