##### Initial conservative management (group B)

Patients randomized to group B will be conservatively managed on a clinical medium neurocare ward or intensive care unit using a TBI treatment protocol based on the BTF. On the ICU, the diagnostic and therapeutic options include ICP monitoring with medical management of intracranial hypertension (i.e., hyperosmolar therapies, hyperventilation) and CPP guided treatment. On the ward, monitoring increased ICP by clinical observation can include waking the patient on predefined time points (every hour during the first 24 to 48 h). Patients initially randomized to group B, who experience significant neurological deterioration, defined as a decrease of GCS score of ≥3 points, will receive delayed secondary hematoma evacuation after a repeated CT scan as deemed necessary by the treating neurosurgeon and will stay within group B as this is an ITT design. Similarly, group B patients who undergo secondary burr hole drainage within 6 months after initial trauma will be analyzed as a subgroup within group B. Alternatively, on the discretion of the treatment team (neurosurgeon, ICU doctor, and neurologist) and communication with the family it can be decided that “comfortable end-of-life care” is more appropriate than surgery. The principle that “the interest of the patient always prevails over those of science and society” will apply in this study.

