#### Other study parameters

With regard to the second research question, the investigators aim to identify subgroups of patients who will benefit substantially from one of the proposed treatments. It should be noted that these subgroup analyses are explorative in nature as this trial has been powered based on the primary effect estimate.

The following subgroups will be investigated:
Elderly with accompanying cerebral contusions visible on first CT versus isolated ASDHs“Younger elderly” (aged 65–80 years) versus “older elderly” octogenarians (aged > 80 years)Elderly receiving specific oral anticoagulants or antiplatelets versus elderly not receiving such medication*Pre-trauma premorbid functionally independent of minimally dependent elderly (FIM score 4–7) versus functionally dependent elderly (FIM score 1–3) [69, 81]Elderly with severe comorbidities (ASA III-V) versus elderly with mild or no comorbidities (ASA I/II) [82, 83]Male versus femaleSurgical technique: basic hematoma removal by craniotomy versus add-on decompressionNo ICP monitoring versus ICP guided treatment taking into account cerebral perfusion pressureSubgroups stratified on (automatically generated) measurements of volumes and ratio of volumes of important intracranial traumatic findings on non-contrast CT in the acute phase

*A subdivision will be made between anticoagulants (e.g., coumarin derivatives/heparin/DOACs) and antiplatelets (e.g., aspirin/clopidogrel/dipyridamole).

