### Sample size {14}

The sample size of 300 patients was based on an ordinal analysis method of the primary outcome. It was calculated analytically using PASS software version 11 and achieves a 90% power to detect a change in the log odds ratio of 0.69 with a 0.05 (two-sided) significance level, allowing for a loss of follow-up of 8%. Calculations were based on the expected percentage distribution of conservatively treated patients over the GOS-E categories 1–8 (15, 10, 10, 10, 10, 10, 15, 20) with category 1 and 2 combined and an estimated (adjusted) proportional odds ratio of 2.0 representing the targeted treatment effect that is considered clinically relevant in the management of elderly with a traumatic ASDH. Table 4 shows the corresponding distribution of patients over the GOS-E outcome categories. The rationale for combining GOS-E categories 1 and 2 in the statistical analysis is the opinion of the researchers that a potentially large shift of patients from category 1 (death) to category 2 (vegetative state) should not result in a positive trial as this cannot be considered a beneficial or positive effect of surgery.

**Table 4 Tab4:** Estimated shift over GOS-E outcome categories

GOS-E	1&2	3	4	5	6	7	8
Patient’s condition	Dead and vegetative state	Lower severe disability	Upper severe disability	Lower moderate disability	Upper moderate disability	Lower good recovery	Upper good recovery
Initial conservative treatment (%)	25	10	10	10	10	15	20
Early surgery (%)	14	7	8	9	10	19	33

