#### Secondary study parameters

For all secondary study parameters, subjects in both arms of the study will be compared using the appropriate tests, based on the ITT population. Graphic data displays may also be used to summarize the data. Statistical analyses may include logistic and linear regression models, Fisher’s exact tests, or chi-square tests and Student’s *t* tests or Mann-Whitney *U* tests (depending on normality of data). The interaction of different operative techniques with treatment arm outcome will be addressed in our subgroup analysis by a Cox Proportional Hazard model with the “day of discharge from the rehabilitation center, nursing, or hospital facility to the own home” as an endpoint/event, which is considered a relevant endpoint from both a QOL and a health-economic perspective. Importantly, analyses of subgroups representing dichotomized continuous variables may also be performed by an interaction-effect analysis.

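### The technique-by-arm interaction and two of the nine subgroups rest on factors decided after randomisation, so they cannot show which patients benefit from early surgery

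*Protocol article*

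**What the plan says.** The second research question (protocol article, Proposed study rationale) asks which patients benefit in interaction with one of the two strategies. It gives three examples: anticoagulant use before the trauma, bony decompression, and ICP monitoring. Other study parameters lists nine subgroups and calls their analysis explorative. Two of the nine are surgical technique ("basic hematoma removal by craniotomy versus" added decompression) and monitoring (none versus "ICP guided treatment taking into account cerebral perfusion" pressure).

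Secondary study parameters names the model: "The interaction of different operative techniques with treatment arm outcome will be addressed in our subgroup analysis by a Cox Proportional Hazard model". The event is the day of discharge to the patient's own home.

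The intervention sections say how these factors arise. Technique is left to the surgeon and local practice. In general a craniotomy is done, and "DC when (intractable) swelling is seen intra-operatively or when swelling is expected (preventive"). In group B, evacuation follows only after neurological deterioration, as the neurosurgeon judges necessary. The same section adds that "group B patients who undergo secondary burr hole drainage within 6 months after initial trauma will be analyzed as a subgroup within group B".

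On the entry population, Proposed study rationale says that "an important subgroup of comatose patients with a small traumatic ASDH < 10 mm and a midline shift < 5 mm will be included". This route (GCS below 9, small lesion) is not among the nine subgroups. GCS enters the primary model as a covariate only.

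**The concern.** A subgroup factor can show who benefits from a randomised treatment only if allocation could not have influenced it. Technique and ICP monitoring do not meet that condition. Decompression is partly a marker of swelling and hence of severity. Monitoring is chosen in a different setting in each arm: alongside surgery in group A, as part of ICU care in group B. For most of group B, technique does not exist.

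A report that decompression or monitoring modifies the benefit of surgery could therefore show only that sicker patients were managed differently. Existing research evidence, in the same article, criticises earlier studies for this kind of selection. The stakes go beyond a footnote: the second research question names both factors, and Implementation of study results plans a decision aid for patients and clinicians based on the trial's findings.

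**Working it through.** **1. The plan's own figure.** Sample size {14} says that 300 patients "achieves a 90% power to detect a change in the log odds ratio of 0.69 with a 0.05 (two-sided) significance level". It assumes that 8% of patients are lost. Inputs: control distribution 25/10/10/10/10/15/20% and odds ratio 2.0, which gives a surgery distribution of 14.3/6.9/7.8/8.9/10.2/18.5/33.3%. With p̄ the mean of the two distributions, 1 − Σp̄³ = 0.966.

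N = 12(1.960 + 1.282)² / [0.69² × 0.966] ≈ 274.3, so 275 evaluable; 275/0.92 = 298.9, so 299.

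The stated 300 is reproduced. Evaluable patients: 300 × 0.92 = 276, or 138 per arm, with power 90.2%. Nothing below changes this.

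**2. Timing of the nine factors.** Seven are baseline: contusions, age, anticoagulant or antiplatelet use, FIM, ASA, sex, acute CT volumes. Two are set after allocation: technique and ICP monitoring.

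**3. Estimability of technique by arm.** Model columns: intercept, arm, craniotomy (CR), decompression (DC), arm×CR, arm×DC.

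| Cells with patients | Rank |
|---|---|
| A-CR, A-DC, B-unoperated | 3 of 6 |
| the same plus B-CR, B-DC (delayed surgery) | 5 of 6 |
| the same plus some unoperated group A patients | 6 of 6 |
| operated only: intercept, arm, DC, arm×DC | 4 of 4 |

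Against unoperated group B patients the interaction terms cannot be estimated. They become computable only through cells that post-randomisation events create: deterioration in B, or not receiving the allocated surgery in A.

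**4. Precision among operated patients.** Assumptions, none given in the article: 10–30% of group B has delayed surgery, 20–40% of operated patients have DC, 60% are discharged home. With e = 0.6, n_A = 138, n_B = 138 × the delayed share, and q the DC share:

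SE² = 1/(e·n_A·q) + 1/(e·n_A·(1−q)) + 1/(e·n_B·q) + 1/(e·n_B·(1−q))

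- 10% delayed, 20% DC: n_B = 13.8, SE = 0.911, detectable ratio at 80% power = exp(2.80 × 0.911) ≈ 12.8.
- 30% delayed, 40% DC: n_B = 41.4, SE = 0.467, detectable ratio = exp(2.80 × 0.467) ≈ 3.7.

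**5. Illustration of selection.** This is a simulation of 2,000,000 patients in which neither surgery nor technique has any effect. Severity alone drives decompression, deterioration and time to home. The assumed coefficients give 19% of B operated and 30% DC in A. Rate ratios for going home:

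- All A versus all B: 1.00
- A-DC versus all B: 0.68
- A-CR versus all B: 1.19
- Operated only, A versus B: 1.55 within CR, 1.45 within DC

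Every departure from 1 is selection. In this set-up the ratio of the two operated-only figures is about 0.93 (1.446/1.550). The example therefore shows large bias in the technique-specific effects of surgery; it does not fix the size of bias in the interaction term, which depends on how decompression is chosen in each arm.

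**6. What a valid baseline interaction could show.** With V = 12/0.966 = 12.43 and a subgroup share f of 276 patients, SE² = V/(276f) + V/(276(1−f)). Power to detect a ratio of odds ratios of 2:

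| Split | SE | Power |
|---|---|---|
| 50/50 | 0.424 | 37% |
| 20/80 | 0.531 | 26% |
| 10/90 | 0.707 | 16% |

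**The case against.** The best defence is that these analyses are labelled explorative, that the trial is powered for the primary estimate only, and that most of the subgroup plan is sound. That is right about scope. The label, however, answers low power and multiple testing; it does not answer confounding.

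Several stronger readings are tempting, and the documents do not support them:

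- **That the second research question rests on post-randomisation subgroups.** Seven of the nine are baseline, and one of the question's three examples is use of anticoagulants before the trauma.
- **That the technique-by-arm term is unidentifiable at any sample size.** Delayed evacuation in group B makes a DC-versus-CR by arm contrast computable. The fault is what it compares, and its imprecision.
- **That burr-hole drainage is a proposed effect modifier.** It is a separate analysis within group B, absent from the list of nine and not tied to the second research question.
- **That omitting entry route is an error, or that it erodes the power of the primary test.** Route is part of eligibility, not a randomisation stratum (randomisation is stratified by centre). GCS is already a covariate, and CT volumes on the list touch lesion size. The article gives no share, outcome distribution or treatment effect for comatose patients, so no dilution figure can be derived from it. The subgroup could also be specified in an analysis plan not shown here.

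The plan also already allows interaction analyses for subgroups that dichotomise a continuous variable.

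**Conclusion.** The point holds for one stated model and two listed subgroups. The technique-by-arm Cox interaction cannot be estimated against unoperated group B patients. Among operated patients it compares nearly all of group A with a part of group B selected by deterioration, so it cannot be read as effect modification. Technique and ICP monitoring fail as effect modifiers for the same underlying reason: they are chosen after allocation, partly on severity.

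The estimability result follows from the design alone, given that group A is operated as allocated. The detectable ratios of 3.7 to 12.8 and the simulated rate ratios rest on assumed rates and are illustrative. The consequence is limited to exploratory inference on the second research question; the primary analysis and the sample size stand. This should be fixed, but it does not threaten the trial's main result.

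**What to change.** - In Secondary study parameters, drop the technique-by-arm Cox interaction.
- In Other study parameters, take technique and ICP monitoring off the list of factors meant to identify who benefits. Report them, and the burr-hole subgroup within group B, descriptively and labelled as non-randomised comparisons. Align the examples in the second research question.
- Test the baseline subgroups by a treatment interaction term in the adjusted proportional odds model for GOS-E, keeping age and CT volumes continuous.
- As an exploratory addition, include entry route (GCS below 9 with a small lesion versus GCS 9 or above) as a treatment interaction, since the article itself calls the comatose group important.

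The cost is wording in the protocol and analysis plan. GCS and lesion size are already recorded for eligibility, so no new data are needed. The downside is imprecision: if the comatose share were 10–20% (an assumption), power for a ratio of odds ratios of 2 would be only 16–26%. The route result should therefore be given as an estimate with its interval, and an absence of significance should not be read as absence of a difference.

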### Interim analyses {21b}

This is not applicable; no interim analyses will be performed.

### Methods for additional analyses (e.g., subgroup analyses) {20b}

A cost-effectiveness analysis (CEA) and a cost-utility analysis (CUA) will be conducted to identify the costs per quality-adjusted life year (QALY) gained for both the surgically treated and the conservatively managed group [91].

#### Economic evaluation

An economic evaluation will be performed in accordance with the Dutch and Belgium guidelines for economic evaluations [92, 93]. It will be performed from a healthcare and societal perspective and will be estimated for a short-term (1 year) and long-term (5 years) period. A cost-effectiveness analysis (CEA; with GOS-E at 1 year as outcome) and a cost-utility analysis (CUA; with QALY as outcome) will be performed. With a decision model, the effectiveness in quality-adjusted life years (QALYs) [91], the costs, and the cost-effectiveness ratios (Euros/QALY) will be calculated for the long-term, using data from this study in combination with literature data.

#### Cost analysis

The cost analysis from the healthcare perspective will include direct healthcare costs, induced (indirect) healthcare costs (events, admissions, follow-up visits, follow-up procedures), and direct non-healthcare costs (patient time costs, out-of-pocket, and travel expenses). Resource utilization will be determined through documentation in the CRF. Hospital acute care costs will be calculated using reference prices as described in the national guidelines for healthcare costs research [92, 93]. The costs of post-discharge long-term care and rehabilitation care will be calculated by a similar method. Indirect costs as well as other direct non-medical costs will be obtained from patients or caregivers by questionnaires. Intramural care costs, patient costs and productivity loss of both patient and family will be determined through tailored patient questionnaires containing the relevant aspects of the iMCQ, iPCQ, and iVIC questionnaires. These questionnaires will be conducted by live visits or telephone interviews at 3 months, 6 months, 1 year, and 5 years follow-up. Costs of the interventions will be determined with extensive cost analysis enumerating costs of the equipment, personnel, materials, administration, and overhead. In Belgium, the national registry of intramural care will be used to validate parts of our questionnaire regarding healthcare use. Costs of complications and events during follow-up will be estimated. Importantly, previously neglected variables in the elderly population like familial childcare, retirement spending habits, volunteer work, or loss of productivity of caregiving family members will also be considered in the cost analysis.

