#### Secondary study parameters/endpoints

Secondary outcomes will be measured at 3, 6, 12, 24, 36, 48, and 60 months after randomization. Follow-up at 3, 6, and 12 months will be executed by live visits from research nurses from Leiden/Leuven. Other follow-up moments will be captured by postal or telephone, depending on the clinical state of the patient. As the GOS-E is a global outcome measure, cognitive, physical, social, and psychological disturbances may be insufficiently captured. Therefore, the widely adopted TBI-specific HRQOL questionnaire QOLIBRI [82–84] will also be used as an important secondary outcome. Furthermore, the EuroQol-5D-5L questionnaire will be used for the economic evaluation [85]. Cognitive functioning will be assessed by the Montreal Cognitive Assessment (MOCA) [86]. The four questionnaires are briefly described:

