**Fig. 4 Fig4:**
[figure not shown]
RESET-ASDH study design flowchart

**Table 3 Tab3:** Follow-up valuation

	Patient visit by research nurse				Telephone/postal			
Questionnaires	Discharge	3 months	6 months	1 year	2 years	3 years	4 years	5 years
Demographics	X							
GOS-E The Glasgow Outcome Scale (Extended) is (together with its precursor GOS) the most commonly used global outcome measure in TBI research	X	X	X	X^a^	X	X	X	X
QOLIBRI The Quality of Life after Brain Injury is the first TBI disease-specific quality-of-life outcome tool that is cross-culturally developed and validated in large populations		X	X	X	X	X	X	X
EQ-5D-5L EuroQol-5D-5L is a 5-dimensional generic instrument assessing health-related quality of life and health status and generates an index of health for use in economic evaluations		X	X	X	X	X	X	X
MOCA The Montreal Cognitive Assessment is a widely used questionnaire assessing 8 domains of cognitive functioning. As the MOCA cannot be completed per telephone, it will only be performed during the live visits up to 12 months		X	X	X				
Health economics Intramural care costs, patient costs and productivity loss of both patient and family will be determined through tailored patient questionnaires containing the relevant aspects of the iMCQ, iPCQ and iVIC questionnaires		X	X	X				X

^a^Primary outcome

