#### Cost-effectiveness and cost-utility analysis

An incremental cost-effectiveness ratio (ICER) will be calculated comparing the costs and effects between the surgical and conservative treatment group. A CUA will be performed for which the QALY, calculated based on the EQ-5D-5L summary score, is the outcome measure. For the CEA, the primary effect measure will be the GOS-E. The costs and effects will be discounted. A 1-way, 2-way, and probabilistic sensitivity analysis will be performed to determine the effect of uncertainty in all input parameters.

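### The healthcare perspective includes non-healthcare costs, and the cost questionnaire skips years 2 to 4, so most long-term questionnaire-based costs rest on the decision model and on 5-year survivors

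*Protocol article*

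**What the plan says.** **Perspective and horizon.** The Economic evaluation section states: "It will be performed from a healthcare and societal perspective and will be estimated for a short-term (1 year) and long-term (5 years) period". For the long term, a decision model is declared, whose QALYs, costs and ratios "will be calculated for the long-term, using data from this study in combination with literature data".

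**Cost list.** The Cost analysis section opens with the content of the healthcare perspective. Besides direct and induced healthcare costs, that list includes "direct non-healthcare costs (patient time costs, out-of-pocket, and travel expenses" (the closing bracket falls outside the quote). No separate list is headed as societal.

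**Cost schedule.** Questionnaires supply intramural care costs, patient costs, and lost productivity of patient and family. On timing: "These questionnaires will be conducted by live visits or telephone interviews at 3 months, 6 months, 1 year, and 5 years follow-up". The health economics row of Table 3 agrees: it is marked at 3 months, 6 months, 1 year and 5 years, and empty at years 2, 3 and 4.

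**Utility schedule.** "A CUA will be performed for which the QALY, calculated based on the EQ-5D-5L summary score, is the outcome measure". The outcomes section says: "Secondary outcomes will be measured at 3, 6, 12, 24, 36, 48, and 60 months after randomization". In Table 3 the EQ-5D-5L row is empty at discharge and marked at 3 and 6 months and at every year from 1 to 5. At discharge only demographics and GOS-E are marked.

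**The concern.** Cost-effectiveness is part of the first research question and of the stated hypothesis, so the economic result will be read alongside the clinical one.

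The perspective matters because a healthcare ratio and a societal ratio answer different questions for different payers. If patient time, travel and out-of-pocket spending sit in both, the healthcare figure is mislabelled and the contrast between the two perspectives shrinks.

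The cost schedule matters because the section on possible return of investment argues that surgery may pay off through lower long-term nursing costs and less lost productivity. These are largely the costs that the questionnaires are meant to capture, and between the first and the fifth year they are not asked about. The patients who answer at year 5 are those who lived that long, and the two arms may be selected differently by then. Table 4 targets 25% versus 14% in the combined dead-or-vegetative category at 1 year. That does not isolate mortality, but it shows that the design allows survival to differ by arm.

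**Working it through.** The protocol gives no numerical economic result to reproduce. The check compares the sections with each other and measures the gaps.

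**1. Perspective.** Write ΔH for the between-arm difference in healthcare costs, ΔN for the difference in the items that the protocol calls non-healthcare, and ΔE for the difference in effect.
- Healthcare ratio as its label implies: ΔH / ΔE.
- Healthcare ratio as the Cost analysis section lists it: (ΔH + ΔN) / ΔE.
- Discrepancy: ΔN / ΔE.

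The protocol gives no unit costs or volumes for patient time, travel or out-of-pocket spending, so neither the size nor the sign of ΔN can be stated.

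**2. Cost questionnaire.** Times in years, from the Cost analysis section and Table 3: 0.25, 0.5, 1, 5.
- Longest interval: 5 − 1 = 4 years, which is 4/5 = 80% of the 5-year horizon.
- The recall period of the year-5 form is not given. Assumed 12 months: 4 − 1 = 3.0 years uncovered, 3.0/5 = 60%. Assumed 3 months: 4 − 0.25 = 3.75 years uncovered, 3.75/5 = 75%.
- With forms at years 2, 3 and 4 the longest interval falls from 4 years to 1 year.

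Utility and GOS-E are observed at years 1, 2, 3, 4 and 5, so the long-term gap concerns costs only.

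**3. Utility in the first 3 months.** EQ-5D-5L times: 0.25, 0.5, 1, then yearly.
- Share without a measured utility: 0.25/1 = 25% of the 1-year horizon and 0.25/5 = 5% of the 5-year horizon.
- Trapezoidal weights for a 1-year QALY with a value at time 0: 0.125, 0.25, 0.375 and 0.25 at 0, 3, 6 and 12 months.
- QALY over 0–3 months for a patient alive at 3 months: 0.125 × (u₀ + u₃). With an assumed u₃ = 0.6:

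| Assumed u₀ | 0–3 month QALY |
|---|---|
| −0.3 | 0.0375 |
| 0 | 0.075 |
| 0.3 | 0.1125 |
| 0.6 (3-month value carried back) | 0.150 |
| 1.0 | 0.200 |

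These are levels for one patient, not differences between arms. With the same u₀ in both arms, 0.125 × u₀ cancels among patients alive at 3 months. It does not cancel fully for earlier deaths: on a straight line to zero at death time d, the starting value contributes u₀ × d/2. What remains uncertain is therefore the early course and the early deaths, not a starting difference.

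**The case against.** **The long-term result is declared as a model.** A reader might infer that the schedule cannot support a 5-year result. The protocol does not bear that out: it plans a decision model using trial and literature data, yearly GOS-E and EQ-5D-5L can feed it, and one-way, two-way and probabilistic sensitivity analyses are planned. This stands. It does not remove the point, because sensitivity analysis varies inputs and does not supply missing observations. The return-of-investment section itself says that the fragile elderly were left out of earlier studies, that present costing methods miss contributions of older people, and that caregivers' lost productivity is mostly overlooked. The literature is thus weakest where the model would lean on it.

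**Other cost sources exist.** A reader might infer that years 2 to 4 have no cost data at all. That goes too far. Resource use is also documented in the CRF, with no stated end date, and costs of complications and events in follow-up are to be estimated. Patients who die in years 2 to 5 will have contributed first-year questionnaires, and caregivers may be respondents. What stands is narrower: no cost questionnaire is scheduled in those years, and none is scheduled around a death. Sites follow patients only to discharge, later follow-up is central, and the Belgian registry only validates parts of the questionnaire.

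**Starting utility.** A reader might take an arm difference of, say, 0.05 to 0.20 in starting utility, multiply by 0.125, and report a shift of 0.006 to 0.025 QALY. The design does not support this: under 1:1 randomisation the expected difference at time 0 is zero. Nor would EQ-5D-5L at discharge supply a time-0 value, since discharge follows treatment and its timing varies by patient.

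**National guidelines.** A reader might call the healthcare ratio wrong by definition. The protocol defers to Dutch and Belgian guidelines that are not available here, and these may place an item such as out-of-pocket payments for care within healthcare. That is why the fix allows relabelling.

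**Conclusion.** The point holds in three parts of unequal weight.

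1. The healthcare cost list conflicts with its own label and with the separate societal perspective. The distortion is ΔN/ΔE, which cannot be sized from the protocol.
2. Between year 1 and year 5, 80% of the long-term horizon, no cost form is given. Questionnaire-based costs after year 1 come only from patients followed to 5 years, and 60 to 75% of the horizon falls outside any form if recall is 3 to 12 months (assumption). The result is computable but more dependent on the model and on survivors than it needs to be.
3. Minor: the first 25% of the 1-year QALY period needs an assumed utility. The 1-year result remains computable, with cost forms at 3, 6 and 12 months and hospital care in the CRF.

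The primary endpoint and its analysis are untouched.

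**What to change.** - **Perspective.** Count patient time, out-of-pocket and travel costs in the societal perspective only. Where the cited national guidelines require an item in the healthcare perspective, keep it there and relabel it. Cost: a wording correction.
- **Cost schedule.** Add the health economics questionnaire to the existing telephone or postal contacts at years 2, 3 and 4, and amend Table 3 and the Cost analysis section together. A short form is enough. Cost: a small amendment and somewhat longer contacts, with no new ones.
- **Early utility.** Apply one common starting utility to both arms, and vary that value and the 0–3 month course, including early deaths, within the sensitivity analyses already planned. Cost: no extra data collection.
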